### Eligibility criteria for participants

Participants with pulmonary TB satisfying the inclusion criteria are enrolled competitively by investigators in the outpatient clinic as well as the inpatient setting in the four participating hospitals. The inclusion criteria are as follows: men and women aged from 20 to 80 years, with documented sputum Xpert MTB/RIF® assay-positive pulmonary TB at screening, and administration of current TB therapy (if any) for ≤7 days at the time of enrollment.

Patients will be excluded if they have HIV/AIDS. Female patients of childbearing potential who are pregnant, breastfeeding, or unwilling to avoid pregnancy will also be excluded. Additionally, any of the following factors will lead to exclusion: (1) absolute neutrophil count of <2000 cells/mL, (2) white blood cell count of <3.0 × 10^3^/μL, (3) hemoglobin levels of <7.0 g/dL, (4) serum creatinine levels of >2.0 mg/dL, (5) aspartate aminotransferase levels of >100 IU/L, (6) alanine aminotransferase levels of >100 IU/L, (7) total bilirubin levels of >2.0 mg/dL, (8) history of optic neuritis or peripheral neuropathy, and (9) other significant laboratory abnormalities (i.e., absolute neutrophil count, creatinine levels). Finally, we also exclude patients with the need for ongoing therapy with selective serotonin reuptake inhibitors, tricyclic antidepressants, serotonin 5-hydroxytrptamine 1 receptor agonists (triptans), meperidine, buspirone, monoamine oxidase inhibitors, sympathomimetic agents (e.g., pseudoephedrine), vasopressive agents (e.g., epinephrine, norepinephrine), or dopaminergic agents (e.g., dopamine, dobutamine).

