Sputum AFB smear	X	X^d^	X	X	X	X	X	X	X	X
TB culture (solid)	X	X^d^	X	X	X	X	X	X	X	X
TB culture (liquid)	X	X^d^	X	X	X	X	X	X	X	X
DST^b^	With first cultured *Mycobacterium tuberculosis*									
CXR	X	X^d^			X	X	X	X	X	X
HIV, HBV	X									
Total bilirubin, AST/ALT, creatinine	X	X^d^	X	X	X	X	X	X	X	X
Complete blood count	X	X^d^	X	X	X	X	X	X	X	X
Optic test		X	X	X	X	X				
Urine HCG^c^	X									
Compliance of drug intake			X	X	X	X	X	X	X	X
Adverse drug reaction			X	X	X	X	X	X	X	X
Other medications^e^		X	X	X	X	X	X	X	X	X

*w* weeks, *d* days, *NA* not applicable, *AFB* acid-fast bacilli, *TB* tuberculosis, *DST* drug susceptibility test, *CXR* simple chest radiography, *HIV* human immunodeficiency virus, *HBV* hepatitis B virus, *AST* aspartate transaminase, *ALT* alanine transaminase, *HCG* human chorionic gonadotropin

^a^Treatment will be initiated at the baseline visit, as TB treatment should be started promptly following diagnosis

^b^Drug susceptibility test for isoniazid, rifampicin, ethambutol, pyrazinamide, streptomycin, kanamycin, amikacin, capreomycin, ofloxacin, levofloxacin, moxifloxacin, prothionamide, cycloserine, and *para*-aminosalicylic acid

^c^Only in females of childbearing potential

^d^Can be omitted if the results of previous tests within the prior 4 weeks are available

^e^In particular, immunosuppressive agents (including corticosteroids)

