## Discussion

Development of a shorter duration anti-TB treatment regimen could improve not only treatment outcomes of individual patients but also TB control throughout the world. Based on higher culture conversion rates after 2 months of treatment in drug-susceptible TB patients treated with regimens, including moxifloxacin [9, 10], 4-month regimens, including moxifloxacin or gatifloxacin, have been attempted recently. The REMoxTB trial replaced isoniazid or ethambutol with moxifloxacin [11]. The OFLUOTUB trial used gatifloxacin instead of ethambutol [12]. The RIFAQUIN trial included moxifloxacin instead of isoniazid in the intensive phase and used twice-weekly application of moxifloxacin and rifapentine in the continuation phase [13]. Another trial tested three-times-weekly administration of isoniazid, rifampicin, pyrazinamide, and moxifloxacin or gatifloxacin instead of ethambutol [14]. Unfortunately, none of these 4-month treatment regimens showed non-inferiority to a 6-month regimen.

Based on the impressive effectiveness of linezolid in patients with XDR-TB refractory to previous treatment [6], we are performing a trial using linezolid instead of ethambutol for drug-susceptible pulmonary TB. If a new regimen including linezolid shows an excellent culture conversion rate by week 8, which could be a surrogate for relapse [15, 16], it could be tested as a 4-month anti-TB treatment regimen through another clinical trial.

Safety issues of using linezolid for TB treatment will also be addressed through the current trial. Although linezolid is highly effective for the treatment of multidrug-resistant TB, it is frequently accompanied by serious AEs, including peripheral neuropathy and bone marrow suppression. In a recent clinical trial of linezolid in patients with XDR-TB, as many as 87% of patients reported clinically significant AEs [6]. Similarly, a meta-analysis reported AEs in 58.9% of multidrug-resistant or XDR-TB patients who used linezolid [17]. These reports of frequent AEs underscore the limitation of linezolid as a standard drug for treatment of multidrug-resistant TB, which mandates the long-term use of anti-TB drugs. Our trial using linezolid for 2 or 4 weeks, times which are within the permitted duration of use, will reveal the safety of the relatively short-term use of linezolid for patients with TB.

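### The neutrophil exclusion is printed per mL (2 cells/µL), so the numeric criterion excludes practically no one; its unit must be reconciled, though other blood-count protections remain

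*Protocol article*

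**What the plan says.** The section Eligibility criteria for participants gives nine numbered exclusions, any one of which is enough to exclude. Four bear on this point:

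- Exclusion (1): "absolute neutrophil count of <2000 cells/mL".
- Exclusion (2): "white blood cell count of <3.0 × 10^3^/μL".
- Exclusion (3): "hemoglobin levels of <7.0 g/dL".
- Exclusion (9): "other significant laboratory abnormalities (i.e., absolute neutrophil count, creatinine levels", with no numeric limit. Creatinine already has its own limit in exclusion (4), above 2.0 mg/dL.

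Three other places give context. The Discussion says of linezolid that "it is frequently accompanied by serious AEs, including peripheral neuropathy and bone marrow suppression". The row "Complete blood count" in Table 2 (Design section) is marked at screening, at baseline (which may be omitted if a result from the prior 4 weeks exists) and at every treatment visit. The section Statistical analysis makes meeting the inclusion and exclusion criteria a condition of belonging to the ITT groups.

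**The concern.** Two adjacent limits from one blood count are in units that differ by a factor of 1000. The per-mL unit turns the neutrophil limit into a value that hardly any patient would fall below. No other section states a neutrophil limit that would show which unit was meant.

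Two things are at stake. First, two of the three arms receive a drug that the article itself associates with marrow suppression, so baseline neutrophil eligibility bears on the trial's safety question. Second, the ITT groups are defined partly by the eligibility criteria. A participant with a low neutrophil count but an acceptable white-cell count is therefore inside or outside the primary analysis set depending on how exclusion (1) is read.

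Exclusion (9) names the neutrophil count but gives no limit. With exclusion (1) empty, the only neutrophil screen left is a matter of judgement, exercised at four hospitals that recruit competitively.

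**Working it through.** The neutrophil limit is not derived from other figures in the article, so there is no calculation of the plan's own to reproduce. The check is a unit conversion and a comparison with the neighbouring limit.

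**Inputs** (Eligibility criteria for participants)
- Neutrophil limit, exclusion (1): 2000 cells/mL.
- White-cell limit, exclusion (2): 3.0 × 10^3/µL = 3000 cells/µL.
- Conversion: 1 mL = 1000 µL.

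**Step 1: convert the printed limit.** 2000 cells/mL ÷ 1000 = 2 cells/µL = 0.002 × 10^3/µL.

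**Step 2: ask who could meet exclusion (1) after passing exclusion (2).** With white-cell count W per µL, the printed neutrophil limit is met only if neutrophils are below 2/W of white cells. A patient who passes exclusion (2) has W of at least 3000, so the share is at most 2/3000 = 0.00067, or 0.067%. It falls further as W rises. As printed, the criterion excludes practically no one.

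**Step 3: size of the discrepancy.** Suppose, as an assumption only, that the number 2000 were per µL. It would equal 2000 × 1000 = 2,000,000 cells/mL, which is 1000 times the printed limit and 2000/3000 = 67% of the white-cell limit. The patients whose status would change are those with white cells of at least 3000/µL and neutrophils from 2 up to, but not including, 2000/µL. The article gives no distribution of baseline counts, so their number cannot be calculated. This step measures the discrepancy; it does not say which limit is right.

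**Step 4: is the unit a text-extraction fault?** The µL symbol is rendered correctly in the very next item, so an extraction fault is unlikely.

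**Step 5: what still operates if exclusion (1) is empty.**

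| Provision | Place | Still in force? |
|---|---|---|
| Numeric neutrophil limit | Exclusion (1) | Practically empty as printed |
| White-cell limit | Exclusion (2) | Yes |
| Haemoglobin limit | Exclusion (3) | Yes |
| Neutrophils named, no limit | Exclusion (9) | Yes, by judgement |
| Blood count at each treatment visit | Table 2 | Yes |

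**Step 6: design quantities.** The sample size rests on conversion rates of 75% and 90%, α = 0.05, power of 85%, and 10% allowances for default and for culture failure. No blood-count limit enters it, so sample size, α and power are unaffected.

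**The case against.** The strongest case on the other side is that this is a slip in a journal article and no more. A limit of 2 cells/µL beside a white-cell limit of 3000/µL is so implausible that no site is likely to have applied it. The full protocol and the eCRF limits are not shown and may carry a different unit. Other screening and on-treatment monitoring remain, and the duty physician may stop or modify the regimen for adverse events. Much of this stands: the cause is probably typographical, and there is no evidence that the per-mL limit was used. It does not remove the point. The article states a numeric eligibility limit, states it in a unit that empties it, and offers nothing elsewhere to correct it. That is a wrong statement rather than a detail left to another document.

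Three stronger readings are tempting, and the article does not support them.

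- A reader might infer that blood-count protection as a whole is disabled. Only the numeric neutrophil criterion is. Exclusions (2), (3) and (9) and the scheduled blood counts remain, so passing exclusion (1) is not the same as being enrolled.
- A reader might infer that exclusion (9) contradicts exclusions (1) and (4), and that neutrophils and creatinine should be taken out of it. The exclusions are alternatives. A value that passes a numeric limit but is judged significant under (9) is simply excluded, which is redundant and discretionary but not contradictory. Taking neutrophils out would alter a clinical eligibility rule and delete the only other text that can catch a low neutrophil count. Nor does the article show that sites apply different limits.
- A reader might quote 3000/2 = 1500 as the size of the error. That ratio compares a neutrophil limit with a total white-cell limit. The like-for-like discrepancy between the units is 1000.

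**Conclusion.** The point holds as a unit error in an eligibility limit, and it should be corrected. As printed, exclusion (1) is 2 cells/µL. For anyone who passes the white-cell limit, it could bite only with neutrophils below 0.067% of white cells, which in practice is never. The mismatch with the adjacent criterion is a factor of 1000.

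The consequence is limited. One numeric criterion is emptied, and the other haematological exclusions and the monitoring remain. The error is probably typographical. The number of patients affected, and whether there are any, cannot be known from the article.

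The conversion needs no assumption. The practical importance depends on something not shown: whether the full protocol and the eCRF carry the same unit. If they do not, this is a reporting correction. If they do, the neutrophil criterion was not working at screening, and ITT membership of participants with low counts is open to question.

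**What to change.** 1. Reconcile the unit of exclusion (1) with exclusion (2), the full protocol and the eCRF edit check. The sponsor should confirm the intended limit and correct the text. No clinical threshold is proposed here.
2. Keep exclusion (9), and state how it relates to the numeric limits in exclusions (1) and (4), so that investigators know when judgement applies beyond a stated limit.
3. Only if the check shows that the per-mL limit was actually applied, list the affected participants for the data and safety monitoring board, and settle their ITT status before analysis.

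The cost is a one-line correction, a clarifying sentence and a review of one edit check, plus a data query if step 3 applies. The article appeared in February 2017 and expected recruitment to run until July 2017, so on that timetable a correction could still reach patients being screened.

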### Randomization

We assign participants to study arms using an adaptive stratified sampling method to minimize the imbalance between the numbers of participants in each treatment group over a number of stratification factors: the institution, the presence/absence of cavitation on baseline chest radiographs, and the presence/absence of baseline diabetes mellitus. A centralized web-based system of the Medical Research Collaborating Center of Seoul National University Hospital is used for allocation.

Diabetes mellitus is defined by any one of the following: (1) fasting plasma glucose levels ≥126 mg/dL, (2) random plasma glucose levels ≥200 mg/dL, or (3) the presence of any antidiabetic agent as a concomitant medicine.

### Justification of sample size

The hypothesis of this study is that the use of linezolid instead of ethambutol will increase the sputum culture conversion rate on liquid media after 2 months of anti-TB treatment. A primary comparison will be performed between the control arm and experimental arm 1 (linezolid, 600 mg/day for 4 weeks).

#### Hypothesis for sample size calculation

Ho (null hypothesis): *p*
_t_ = *p*
_c_ (culture conversion rate after 2 months of treatment is not different between the control arm and experimental arm 1 [linezolid for 4 weeks]).

H_1_ (alternative hypothesis): *p*
_t_ ≠ *p*
_c_ (culture conversion rate after 2 months of treatment is different between the control arm and experimental arm 1 [linezolid for 4 weeks]).

#### Assumptions

The sputum culture conversion rate on liquid media after 2 months in patients who are treated at Seoul National University Hospital is approximately 75% [8]. We assume that there will be a 90% culture conversion rate on liquid media after 2 months in experimental arm 1 (primary hypothesis) and a 10% default (loss to follow-up) rate, and that 10% of participants will have a positive Xpert MTB/RIF® assay result but a negative result for *M. tuberculosis* culture.

Based on an α = 0.05 level of significance, a power of 85%, and a 15% difference in the culture conversion rate after 2 months between the control arm and experimental arm 1 (75% vs. 90%), the sample size per arm was calculated to be 114 (342 in total). After consideration of a 10% default rate and 10% culture failure in participants with a positive Xpert MTB/RIF® assay result, the final number per arm was calculated to be 143 (429 in total).

### Statistical analysis

The results of this trial will be analyzed based primarily on the intention-to-treat (ITT) approach. In addition, a per protocol analysis will be performed secondarily. A safety analysis will be performed based on the safety group. The ITT groups will comprise participants who satisfy the inclusion and exclusion criteria, those who are randomized, and those who take the trial drug at least once. The per protocol groups will comprise participants from ITT satisfying the following conditions: (1) participants took the trial drug (ethambutol or linezolid) at greater than 80% of the planned dose (ethambutol, ≥45 days for control arm; linezolid, ≥23 days for experimental arm 1; linezolid, ≥12 days for experimental arm 2), and (2) participants completed the clinical trial according to the protocol. The safety group includes participants who took the trial drug at least once. No interim analysis of the data is planned.

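### The primary ITT set allows exclusions after randomisation, and the per-protocol set for the week-8 outcome depends on later events; both can bias the comparison, by an amount the protocol does not determine

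*Protocol article*

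**What the plan says.** The Statistical analysis section of the protocol article states: "The results of this trial will be analyzed based primarily on the intention-to-treat (ITT) approach". A per-protocol analysis comes second. The ITT group is then restricted. Participants must satisfy the inclusion and exclusion criteria, and the definition adds "those who are randomized, and those who take the trial drug at least once". I read these as conditions that must all be met.

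The per-protocol definition in the same paragraph shows what trial drug means. Its first condition is that "participants took the trial drug (ethambutol or linezolid) at greater than 80% of the planned dose", with cut-offs of "ethambutol, ≥45 days for control arm; linezolid, ≥23 days for experimental arm 1; linezolid, ≥12 days for experimental arm 2". Its second condition is that "participants completed the clinical trial according to the protocol".

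Other sections give the context:
- Outcomes: the primary outcome is culture conversion on liquid media after 2 months.
- Study timeline (Table 2): consent is at screening, randomisation and start of treatment are at the baseline visit, and the last visit is at week 24.
- Eligibility criteria: prior treatment is allowed, as "administration of current TB therapy (if any) for ≤7 days at the time of enrollment".
- Discussion: the article notes that the trial is open-label and that bias is possible.

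**The concern.** An ITT comparison is protected because membership is settled by randomisation alone. Here two conditions can remove a participant afterwards.

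The first is the one-dose rule. A participant allocated to linezolid who declines it but takes isoniazid, rifampicin and pyrazinamide is out of the primary set, although a week-8 culture can still be obtained. A dosed-only set is usually defended on the ground that blinding makes failure to start unrelated to allocation. That defence is not available in an open-label trial. The second is the eligibility condition. It can remove someone found ineligible after allocation, and one exclusion criterion (other significant laboratory abnormalities) calls for judgement.

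The per-protocol set raises a different problem. Membership can turn on what happens between week 8 and week 24, after the primary outcome is known. The adherence condition also exposes control participants to the risk of failing for longer than linezolid participants. If both sets are selected after allocation, agreement between the two analyses is weak support for the primary result.

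**Working it through.** **The plan's own figures.** Reading 2 months as 8 weeks, 80% of 56, 28 and 14 days is 44.8, 22.4 and 11.2 days. Rounded up, these are the stated 45, 23 and 12 days (45/56 = 80.4%, 23/28 = 82.1%, 12/14 = 85.7%). The sample size also reproduces. A two-sided 5% test of 75% against 90% with 85% power (pooled variance, no continuity correction) needs 114 per arm, and 114/0.80 = 142.5, rounded up to 143. The issue is therefore how the sets are defined, not arithmetic.

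**Dropping never-dosed participants.** Inputs: an all-randomised rate of 90% in experimental arm 1 (the planning value); a never-dosed fraction f, which the document does not give, assumed to be 1% to 5%; and a conversion rate r among them, also assumed. After exclusion the arm's rate is (0.90 − f·r)/(1 − f), so the shift is f(0.90 − r)/(1 − f).

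| r among never-dosed | f = 1% | f = 5% |
|---|---|---|
| 75% (the assumed control rate) | 0.01 × 0.15/0.99 = 0.2 points | 0.05 × 0.15/0.95 = 0.8 points |
| 50% | 0.01 × 0.40/0.99 = 0.4 points | 0.05 × 0.40/0.95 = 2.1 points |
| 0% (extreme) | 0.01 × 0.90/0.99 = 0.9 points | 0.05 × 0.90/0.95 = 4.7 points |

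**Effect on the test at the extreme.** Suppose both arms truly convert at 75% with 143 randomised per arm, and the never-dosed are all in experimental arm 1 and all unconverted. Dropping them creates a false difference of 0.75f/(1 − f):
- f = 1% (about 1 participant): 0.8 points, two-sided rejection probability 0.0525;
- f = 5% (about 7 participants): 3.9 points, rejection probability 0.1218.

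The nominal value is 0.05. If the never-dosed convert at the same 75%, there is no false difference.

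**Per-protocol adherence.** Assume the same constant daily stopping rate in every arm, with a proportion s stopping by day 56. The proportion stopping before the cut-off day d is 1 − (1 − s)^(d/56).

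| s by day 56 | Control (d = 45) | Experimental arm 1 (d = 23) | Experimental arm 2 (d = 12) |
|---|---|---|---|
| 5% | 4.0% | 2.1% | 1.1% |
| 10% | 8.1% | 4.2% | 2.2% |
| 20% | 16.4% | 8.8% | 4.7% |

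Identical stopping behaviour therefore gives different selection by arm.

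**Per-protocol completion.** The primary outcome is at week 8 and the last visit is at week 24. A participant with a valid week-8 result who leaves in month 5 fails the completion condition. The document gives no loss rate after week 8, so the number affected cannot be calculated.

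**The case against.** The strongest reply is that little may turn on this. Consent precedes randomisation and treatment starts at the randomisation visit, so few participants should take no dose. Those who decline linezolid still take three other drugs, so the 75% row is the most natural of the three, and the shift is then under one point. This stands. It limits the size of the problem but does not make the set intention-to-treat.

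The per-protocol analysis is secondary, no decision rule rests on it, and one set also has to serve cure and treatment success, for which week-24 completion is relevant. That also stands, but it is a reason to separate the conditions by outcome.

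The adherence rule is the same proportion of the assigned course in every arm. That is correct: a reader might infer a stricter standard for control, and the text does not support it. Only the time at risk of failing differs.

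A reader might also infer that control participants can hardly fail the one-dose rule because up to 7 days of prior therapy is allowed. The document does not say that prior therapy included ethambutol or that doses before randomisation count.

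**Conclusion.** The point holds in a limited form. The primary set is a modified ITT set under an ITT label, and its exclusions can depend on the arm in an open-label trial. This rests on reading trial drug as the participant's own allocated drug, which is the natural sense but not the literal wording.

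The illustrated shift is 0.2 to 0.8 points if never-dosed participants convert at 75%, with an upper limit of 0.9 to 4.7 points, for an assumed never-dosed fraction of 1% to 5%. Two stronger conclusions are tempting and should not be drawn:
- That the primary set favours linezolid. The direction depends on how decliners fare and on how many are dropped in each arm, and the document gives neither.
- That the 10% default rate, about 14 per arm, measures per-protocol losses after week 8. That figure inflates the sample size for the 2-month outcome and says nothing about later losses.

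The per-protocol set is badly matched to the week-8 outcome, but this affects only a secondary analysis.

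**What to change.** **Primary set.** Define ITT as all randomised participants, analysed as allocated. Exclude only on pre-randomisation data, such as a negative baseline culture, and state a rule for missing week-8 cultures. Report the dosed set as modified ITT, as a sensitivity analysis.

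**Per-protocol set for the week-8 outcome.** Keep the present rule of at least 80% of the allocated trial drug, and require no major protocol deviation up to the culture that decides the outcome. Require 24-week completion only for the cure and treatment-success per-protocol analysis. Note that the adherence windows differ by arm, and read the result as supportive only.

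**A change to avoid.** Do not replace the adherence rule with 80% of all intensive-phase doses. With one daily dose per drug, the three shared drugs give 3 × 56 = 168 doses. A participant taking no linezolid would qualify in experimental arm 1 (168/196 = 85.7%) and in experimental arm 2 (168/182 = 92.3%), while a control taking no ethambutol would fail (168/224 = 75%).

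**Cost.** Mostly wording, and drug reconciliation already takes place at every visit. Widening the set does not by itself change 114 or 143 per arm. If 75% against 90% holds among dosed participants and 1% to 5% of experimental arm 1 are never dosed but convert at 75%, the 15-point difference becomes 15 × (1 − f) = 14.9 to 14.3 points. The missing-culture rule matters more. Counting the assumed 10% of defaulters as unconverted gives 67.5% against 81.0%, and about 129 culture-positive participants per arm (143 × 0.9) then give roughly 70% power. The rule should be chosen with that in view.
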